#### Data auditing

This trial will be audited by the Research Ethics Committee and the China Food and Drug Administration. The audits will be performed when the first participant enrolls, and when half and all of the enrolled cases are completed.

### Statistical considerations

#### Sample size

The sample size was calculated based on the primary outcome measure according to the results of our pilot study. Power was set at 80% and calculated based on two-sided 95% confidence intervals. In our pilot data, we detected a post-treatment difference in PD symptoms of at least 20% between the VFS and CFS groups for SWS scores. We assume that the placebo effect can account for about 10% of such differences. We assume that 10% of the trial participants will be lost to attrition. Thus, 53 participants need to be allocated to each treatment group to establish a difference among the treatments at a level of 5% with a power value of 90%.

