### Patient population and recruitment

We intend to enroll a total of 106 participants aged over 18 years. The prospective cohort will comprise patients with PD who have received STN-DBS treatment and have implanted impulse generators that are compatible with VFS (PINS Medical).

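### The sample-size paragraph gives two powers, 80% and 90%, for the single calculation that ends in 53 per group, and does not state the net target difference

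*Protocol article*

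**What the plan says.** All of the relevant text is in the protocol article, mostly under Sample size.

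- Opening statement on power: "Power was set at 80% and calculated based on two-sided 95% confidence intervals".
- Pilot result: "we detected a post-treatment difference in PD symptoms of at least 20% between the VFS and CFS groups for SWS scores".
- Placebo allowance: "We assume that the placebo effect can account for about 10% of such differences".
- Attrition: "We assume that 10% of the trial participants will be lost to attrition".
- Resulting size: "53 participants need to be allocated to each treatment group".
- Closing statement on power, attached to that size: "to establish a difference among the treatments at a level of 5% with a power value of 90" per cent.

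Patient population and recruitment gives the matching total: "We intend to enroll a total of 106 participants aged over 18 years". Data analysis names t tests for continuous variables and the intention-to-treat principle. Handling of missing data specifies carrying the last visit forward. The Discussion lists the power calculation among the strengths of the study.

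**The concern.** The section reports one calculation for the primary outcome, based on one pilot and one significance level (a two-sided 95% interval is the 5% level). It nevertheless names 80% at the start and 90% at the end. No second endpoint or scenario comes between them.

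The effect being powered for is also left open. The pilot difference and the placebo allowance are given, but the difference that remains after the allowance is not. Nor does the section say whether the 20% is relative or absolute.

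At stake is the risk of missing a real effect, which readers will take from this section. It is 20% on one statement and 10% on the other. If the lower power is the true one, a null result would carry a claim of sensitivity that the design does not have.

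**Working it through.** **Inputs.** From Sample size: 53 per group, 10% attrition, two-sided 5% level, powers of 80% and 90%, pilot difference of 20%, placebo share of about 10%. From Randomization and blinding: 1:1 allocation. From Data analysis: t test.

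**Step 1: the plan's own figures.**
- Total: 2 × 53 = 106, as stated.
- Attrition: 47 / 0.9 = 52.2, rounded up to 53; or 48 × 1.1 = 52.8, rounded up to 53. The figure of 53 therefore fits a 10% allowance on 47 or 48 evaluable per group.
- The 53 cannot be derived forward, because the article gives no standard deviation or standardised effect. An article may leave these to the full protocol, so this is a limit on the check and not a criticism of the plan.

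**Step 2: can the attrition allowance explain two powers?** No. Enrolling n / 0.9 restores the planned power after losses; it does not raise 80% to 90%. For a fixed effect, standard deviation, level and n there is one power.

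**Step 3: what the two powers mean at this sample size.** The standardised difference d detectable with n per group is approximately (z₀.₉₇₅ + z_power) × √(2/n).
- n = 47, 80%: (1.960 + 0.842) × √(2/47) = 0.578
- n = 47, 90%: (1.960 + 1.282) × √(2/47) = 0.669

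The exact values for the t test, from the noncentral t distribution, are:

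| Analysed per group | d at 80% | d at 90% |
|---|---|---|
| 47 | 0.584 | 0.676 |
| 48 | 0.578 | 0.669 |
| 53 (all analysed) | 0.549 | 0.636 |

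**Step 4: the gap in participants**, starting from 47 evaluable.
- If 53 was sized for 80% (d = 0.584), 90% power needs 63 evaluable per group. Enrolled: 63 / 0.9 = 70 per group, 140 in total against 106.
- If 53 was sized for 90% (d = 0.676), 80% power needs 36 evaluable per group. Enrolled: 36 / 0.9 = 40 per group, 80 in total.

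**Step 5: the net target.**
- Literal reading, 10% of the difference: 20 − 0.10 × 20 = 18.
- Alternative reading, 10 percentage points: 20 − 10 = 10.

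Illustration only. It assumes that the difference is in percentage points and that the standard deviation is the one at which 47 per group gives the named power for a 20-point difference.

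| Assumed power at 20 points | Implied SD | Power at 18 | Power at 10 |
|---|---|---|---|
| 90% | 20 / 0.676 = 29.6 | 83% | 37% |
| 80% | 20 / 0.584 = 34.2 | 71% | 29% |

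The document supports neither standard deviation. The table shows only that the choice of target matters.

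**The case against.** The strongest reply is that this is a wording slip with no consequence for conduct. The endpoint, the level, the allocation and N are unaffected, the two statements of N agree, and 53 fits the attrition allowance. The 80% may be the leftover figure, in which case 53 is more than 80% power requires. A null result would in any case be judged mainly from its estimate and confidence interval. Much of this stands: the document does not show which figure is the slip, and the harm is conditional on its being the 90%. It does not remove the contradiction in a calculation that the article presents as a strength.

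Three further objections narrow the point.

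- **Standard deviation.** Its absence is not a fault in a condensed article. This stands, and nothing in the conclusion depends on it.
- **Placebo sentence.** The wording speaks of a share of the difference, so 18 is the literal result. The 10-point reading, and the 37% power that goes with it, need a looser reading together with an assumed scale and standard deviation. This stands.
- **Number analysed.** Intention-to-treat with carry-forward would keep dropouts in the comparison, so 53 rather than 47 may be analysed. This stands as an alternative, and both are shown above. Carried-forward values may dilute the effect, so 47 remains a reasonable planning figure. The gap between the two powers remains in either case.

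A reader might infer that the trial is underpowered, or that 140 participants are needed. The document does not support this: the 140 follows only if 53 was sized for 80% and 90% is nevertheless wanted.

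**Conclusion.** The point holds as an internal contradiction. One calculation carries two powers, and one of them must be wrong. The net target after the placebo discount is not stated either; literally it is 18%.

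At this sample size the two powers differ by about 0.09 in detectable standardised difference: 0.58 against 0.68 with 47 per group, or 0.55 against 0.64 with 53. If 53 was sized for 80%, the stated 90% is false and the type II error is twice what that figure implies. If it was sized for 90%, the opening sentence is wrong and the closing claim stands.

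These values assume a two-sided 5% two-sample t test with equal groups, and they need no standard deviation. The illustrative powers for 18 and 10 points rest on assumed scales and standard deviations and are not findings about this trial. Whether 106 is enough cannot be decided from this document.

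**What to change.** Go back to the original calculation and state the single power it used. If it was run at 80%, replace the closing 90% with 80%. If it was run at 90%, replace the opening 80% with 90%.

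In the same paragraph, state the target difference that remains after the placebo discount and its scale: relative or absolute, and seconds or score. It would also help to say whether the power refers to participants remaining after attrition or to all 53 per group, since the planned analysis retains dropouts.

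Keep N = 106. The cost is the rewording of one paragraph, with no added participants and no change to conduct or analysis. The stated power may become less favourable. The article reports that enrolment is still under way, with 50 enrolled, so the correction can be made before results are known.

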#### Data analysis

All evaluations of effectiveness and safety will be conducted according to the intention-to-treat principle. The final data will be analyzed using IBM SPSS 13.0 or higher (SPSS, Inc., Chicago, IL, USA) and SAS 9.4 or higher (SAS Institute Inc., Cary, NC, USA). A *p* value <0.05 will be considered statistically significant. Data will be analyzed with *t* tests and χ^2^ tests for continuous variables and categorical variables, respectively.

### Confidentiality

When participating in research there is always a risk regarding the confidentiality of information. All information gathered in the present study will be stored in a secure database. All participants will provide written informed consent prior to being assessed for eligibility for inclusion in any part of the study. Every precaution will be taken to respect the privacy of participants in the conduct of the study. Information will be stored on a password-protected server with access that is limited to members of the study team. In the course of monitoring data quality and adherence to the study protocol, the monitors will refer to medical records at the participating hospitals. All individual and site information will be de-identified when reporting the data and results to protect the confidentiality of the participants.

## Discussion

Axial and appendicular motor symptoms severely affect the quality of life of patients with PD. DBS is an effective and well-established therapy for medication-refractory patients with PD. High-frequency DBS is highly efficacious in ameliorating appendicular symptoms in patients with PD, but is less effective in improving axial symptoms, especially on a long-term basis [5]. New conceptions of DBS have focused on the use of LFS or combined STN/substantia nigra pars reticulata DBS for the treatment of axial symptoms in patients with PD [6, 9, 10]. LFS may help improve postural control as well as gait, particularly in patients with PD who do not develop gait-related disorders after HFS [11]. However, the beneficial effects of LFS on axial symptoms remain controversial [12]. Therefore, the development of novel approaches to manage both axial and appendicular motor symptoms in patients with PD is critical. Based on these findings and our previously published case report [8], we hypothesize that patients with PD and FOG might benefit from STN-VFS. This multicenter, double-blind, randomized clinical trial will enable us to evaluate the effect of a novel STN-VFS stimulation pattern on both axial and segmental symptoms of PD. This study was designed to evaluate the short-term effects and potential side-effects of VFS and CFS on axial symptoms in advanced PD. We hope to gain insight regarding whether VFS or CFS is more effective for treating axial symptoms of PD. This study has several strengths. First, group assignment in the double-blinded phase was randomized. Second, we performed a power calculation for this study. Most important of all, this new paradigm possibly offers an approach that could optimize DBS programming and improve PD DBS outcomes. At present, the total number of patients enrolled in the study is 50.

### Trial status

The trial is ongoing and is actively enrolling. The protocol version is 1.1, PINS-VFS-1601, 10 November 2016. The trial will be ongoing from August 2017 to December 2019.

## Data Availability

Data from this randomized controlled study are unavailable at the time of publication. Individual participant data are available upon request.

## Abbreviations

AE: Adverse event
CFS: Constant frequency stimulation
CRF: Case report form
DBS: Deep-brain stimulation
DSMB: Data and Safety Monitoring Board
FOG: Freezing of gait
HFS: High-frequency stimulation
LFS: Low-frequency stimulation
PD: Parkinson’s disease
SAE: Serious adverse event
SPIRIT: Standard Protocol Items: Recommendations for Interventional Trials
STN: Subthalamic nucleus
SWS: Stand–walk–sit
UPDRS: Unified Parkinson’s Disease Rating Scale
VFS: Variable-frequency stimulation
